### **8.1.10 Frequency of tumor re-evaluation**

Frequency of tumor re-evaluation by imaging while on treatment and follow-up (if applicable) is once every 2 cycles (56 days). Patients whose efficacy is assessed as CR, PR, or SD will be followed every 2 cycles after discontinuation of treatment until PD, initiation of a new anti-

[figure not shown]

tumor therapy, or withdrawal of consent, whichever occurs first. Some non-target organs may be evaluated less frequently. For example, bone scan re-evaluation may only be required if the target lesion is confirmed as CR or if progression of the bone lesion is suspected.

#### **8.1.11 Response confirmation**

All responses [PR and CR] must be confirmed by a repeat assessment not less than 4 weeks and theoretically not later than 5 weeks after the response criteria are met for the first time.

[figure not shown]

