14. Premenopausal women of childbearing potential must have a negative pregnancy test within 7 days before the treatment.
15. Tumor imaging assessment: Assessments of tumor response will be performed during the screening period (within 3 weeks prior to the first dose), within 7 days prior to Day 1 of Cycles 3, 5 and odd-numbered cycles thereafter, and at the EOT (if it is > 28 days from the last assessment). All responses [PR and CR] must be confirmed by a repeat assessment not less than 4 weeks and theoretically not later than 5 weeks after the response criteria are met for the first time. During the follow-up period after discontinuation, subjects who have discontinued HQP1351 before PD will be assessed for tumor response every 8 weeks (visit time window +/-5 days) until PD or the start of other antitumor therapy, unless the subject voluntarily withdraws from the study. The same assessment method should be used at baseline and subsequent visits. If a subject experiences dose adjustment or interruption, the frequency of imaging examinations or scheduled imaging dates should not be changed. If there are clinical indications, a bone scan may be performed during screening.
16. The baseline collection time is from the screening period to the first dose of HQP1351 in Cycle 1. Sample collection time point for exploratory biomarker analysis is shown in Table 6.
17. PK blood samples will be collected from the first 3 adult subjects in each dose group, and PK blood samples will be collected from all non-randomized adult subjects receiving a fixed dose of 40 mg QOD. PK samples collected from adult subjects at each time point will be about 4 ml. PK sampling time points are shown in Table 5a. PK blood samples will be collected from all adolescent subjects. About 2 ml of blood sample needs to be collected at each PK time point. The PK blood collection time points are shown in Table 5b.
18. AEs will be collected from the time when the subject signs the ICF to 30 days after the last dose.
19. If the laboratory results at screening are within 7 days prior to the first dose of HQP1351, the test will not be repeated on C1D1.

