### **8.1.9.3 Best overall response: all time points**

The best overall response is determined once all the data for the patient is known. The best overall response of the study is defined as the best response across all time points (for example, a patient who has SD at first assessment, PR at second assessment, and PD on last assessment has a best overall response of PR). When SD is believed to be best response, it must also meet the protocol specified minimum time from baseline. If the minimum time is not met when SD is otherwise the best time point response, the patient's best response depends on the subsequent assessments. a patient who has SD at first assessment, PD at second and does not meet minimum duration for SD, will have a best response of PD. The same patient lost to follow-up after the first SD assessment would be considered not evaluable.

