#### Definition of efficacy:

**Objective response rate (ORR):** Defined as the percentage of subjects with confirmed best overall response of complete response (CR) and partial response (PR) (evaluated as per RECIST v1.1 by the investigator).

- When calculating ORR, PR and CR confirmed prior to any other antitumor therapy should both be counted as responses, regardless of how many assessments are missing prior to response.
- According to RECIST v1.1, patients whose best overall response is “unknown” or “not evaluated” will be considered as non-responders for ORR estimation.

[figure not shown]

- Patients who develop PD and continue to receive the study treatment after PD will be considered to have PD at the time the progression is determined, and will be counted for PD and regarded as non-responders for ORR and other efficacy calculations.

**Clinical benefit rate (CBR):** Defined as the proportion of patients with a complete response (CR), partial response (PR), and stable disease (SD) for  $\geq 16$  weeks.

**Duration of response (DOR):** In patients with a response (PR or CR) (as per RECIST v1.1), DOR is defined as the time between the date of the first documented response (PR or CR) and the date of the first documented PD or the date of death from any cause. The censoring rules for DOR are the same as the following censoring rules for PFS.

**Progression-free survival (PFS):** Defined as the time between the date of the first dose of HQP1351 and the date of the first documented PD (as per RECIST v1.1) or the date of death from any cause.

Patients who do not have PD or death as of the analysis cutoff date, or who do not have PD when starting any further antitumor therapy, will be censored at the last adequate tumor assessment prior to the cutoff date, or prior to the date of antitumor therapy.

**Overall survival (OS):** Defined as the time interval from the first dose of HQP1351 to death due to any reason.

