##### **10.4.2 Efficacy analyses**

All efficacy evaluations (ORR, CBR, DOR, PFS, OS) will be analyzed according to the investigator's evaluation (in accordance with RECIST v1.1). The ORR for all responses [PR and CR] must be confirmed by a repeat assessment not less than 4 weeks and theoretically not later than 5 weeks after the response criteria are met for the first time. All efficacy analyses will be based on FAS, and efficacy analyses based on PPS will also be performed as supporting analysis data. All efficacy data will be listed.

The estimate of ORR and CBR will be calculated and 95% confidence interval (CI) will be provided based on an exact binomial distribution.

The Kaplan-Meier method will be used to estimate the median duration of response and median progression-free survival, and Kaplan-Meier curves will be plotted respectively.

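### The 4-to-5-week response-confirmation window matches no consecutive scheduled scan, so ORR depends on how the window is read, and the best-response example leaves confirmation out

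*Protocol*

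**What the plan says.** The confirmation window appears in four places: the synopsis (Efficacy Analyses), Table 8 footnote 15, Section 8.1.11 and Section 10.4.2. Section 8.1.11 sets it at "not less than 4 weeks and theoretically not later than 5 weeks after the response criteria are met for the first time". Section 10.4.2 ties it to the endpoint, saying of the responses behind ORR that each "must be confirmed by a repeat assessment not less than 4 weeks and theoretically not later than 5 weeks".

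Section 8.1.10 says that the imaging interval "while on treatment and follow-up (if applicable) is once every 2 cycles (56 days"). Section 7.5.1 places on-treatment scans in the 7 days before Day 1 of odd-numbered cycles. The imaging row of Table 8 has entries at screening, Day 1 from Cycle 3 (odd cycles, per the footnote), EOT and follow-up, and no separate confirmation visit.

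ORR in Section 10.2.2 is "Defined as the percentage of subjects with confirmed best overall response of complete response (CR) and partial response (PR"). A counting rule below that definition accepts any PR or CR confirmed before other antitumor therapy starts, and gives no latest date for the confirmation.

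Section 8.1.9 says that best overall response takes account of any confirmation requirement. Section 8.1.9.3 then defines it as the best response over all time points, and its example is a patient who has "SD at first assessment, PR at second assessment, and PD on last assessment has a best overall response of PR".

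**The concern.** The rule and the schedule were not fitted to each other. A patient scanned exactly on schedule cannot confirm a response at the next on-treatment scan within 5 weeks. A response that lasts to that scan has lasted longer than the rule demands, yet read strictly it is unconfirmed. Read loosely, or under the Section 10.2.2 counting rule, it is a response. No section says which reading applies.

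Section 8.1.9.3 errs the other way. Taken alone, it lets a single PR stand as best response. CBR and DOR in Section 10.2.2 are defined on CR and PR without the word confirmed, so an unconfirmed PR could enter both.

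Responders are few, so the classification of one patient is visible in the result.

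**Working it through.** **Inputs**
- Cycle length: 28 days (Section 4.1).
- Scan interval: 2 cycles (Section 8.1.10).
- On-treatment scan: 0 to 7 days before Day 1 of odd cycles (Section 7.5.1).
- Day 1 visit window from Cycle 3: ±3 days (Table 8).
- Scans after discontinuation: every 8 weeks, ±5 days (Table 8 footnote 15).
- EOT scan: done if more than 28 days after the last scan (Table 8 footnote 15).
- Confirmation window: 4 to 5 weeks, i.e. 28 to 35 days.

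**The plan's own figure.** 2 × 28 = 56 days, as Section 8.1.10 states.

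**Gap between consecutive scheduled scans** (56 days plus or minus the allowed shifts)
- Pre-visit imaging window only: 56 − 7 = 49 to 56 + 7 = 63 days.
- Adding ±3 days at each of the two visits: 49 − 6 = 43 to 63 + 6 = 69 days (6.1 to 9.9 weeks).
- After discontinuation: 56 − 10 = 46 to 56 + 10 = 66 days.

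The smallest gap, 43 days, is 8 days beyond the 35-day limit, so no consecutive scheduled pair meets the window. All of them meet a plain minimum of 28 days.

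**Exception.** The date of the EOT scan depends on when treatment stops. It can by chance fall 29 to 35 days after a first response.

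**Effect on ORR.** Section 1.6 reports six wild-type subjects, one with a PR in Cycle 9 that was still a PR at Cycle 13. The protocol does not say whether an extra scan was done; assume that only scheduled scans were. With exact binomial intervals, the method of Section 10.4.2:
- later confirmation accepted: 1/6 = 16.7% (95% CI 0.4% to 64.1%);
- 5 weeks taken as a strict limit: 0/6 = 0% (95% CI 0% to 45.9%).

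One responder is 1/11 = 9.1 percentage points in an 11-patient dose group, 1/20 = 5 points in a non-randomized cohort of 20, and 1/60 to 1/50 = 1.7 to 2.0 points in the planned 50 to 60 subjects.

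**Best response for SD, then PR, then PD, with no repeat PR**
- Sections 8.1.9, 8.1.11 and 10.2.2: not a confirmed response.
- Section 8.1.9.3: best overall response PR.

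The passages give two answers, and only Section 8.1.9.3 stands apart.

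**The case against.** The case on the other side is substantial, and it limits the point.

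- A reader might infer that a response confirmed at 8 weeks fails the rule and is thrown away. The text does not say so. All four places qualify the 5-week limit with *theoretically*, and the Section 10.2.2 counting rule has no upper limit. The treatment of a later confirmation is undefined, not clearly excluded.
- A reader might infer that the window cannot be met at all. Footnote 15 is attached to the imaging row of Table 8 and can be read as calling for an extra scan after a first response. That is a coherent design and needs no fixed visit column.
- A reader might infer that the Section 8.1.9.3 example puts unconfirmed responses into ORR. It does not, because ORR uses confirmed best response and Section 8.1.9 itself invokes confirmation. The example also does not state that no confirming scan took place.
- ORR is a preliminary secondary endpoint in a trial whose primary endpoint is safety. At the January 2021 cutoff, 28 assessed subjects had 10 SD, 18 PD and no response (Section 1.5).
- How late confirmations are classified could be settled in the SAP, which was not available for this review.

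All of this stands. What it leaves is that the protocol itself fixes the window, the scan schedule and the best-response example, and these do not fit together. An SAP could say how to classify a late confirmation. It cannot supply a scan that was not done.

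**Conclusion.** The point holds as a mismatch that needs repair. No consecutive pair of scheduled scans can satisfy a 28-to-35-day window, with every stated window used. Whether a response still present at the next scheduled scan counts towards ORR depends on the force of *theoretically*, which the protocol does not define. The size is one responder at a time: 16.7 points in the six wild-type subjects, and about 2 points in the whole study. The wild-type figure assumes that no extra scan was done. The 43-to-69-day range assumes that the visit and imaging windows add together.

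The Section 8.1.9.3 example is a separate inconsistency. It leaves ORR unchanged, but it leaves room for unconfirmed PRs in CBR and DOR.

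**What to change.** 1. In the synopsis, Table 8 footnote 15, Section 8.1.11 and Section 10.4.2, write: *PR and CR must be confirmed by a repeat assessment at least 4 weeks after first documentation, at the next scheduled scan or an earlier unscheduled one.* Delete the 5-week upper limit.
2. Align the Section 8.1.9.3 example with Sections 8.1.9 and 10.2.2, so that an unconfirmed PR is not a best response of PR. It becomes SD if the minimum SD time is met. State that time: Section 8.1.9.3 relies on one, but the protocol gives none for best response, only the 16 weeks for CBR.
3. In Section 10.2.2, state that CBR and DOR use confirmed responses.

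The changes are to wording only. Two costs should be accepted openly. First, confirmation can come about 4 weeks later at nominal timing (56 − 28 = 28 days); the start of DOR does not move, because it runs from the first documented response. Second, the trial is open-label and a response has already been seen, so the change and its date should be documented, and ORR should also be reported under the current 4-to-5-week window as a sensitivity analysis.

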## 9 Adverse events (AEs) and serious adverse events (SAEs)

The investigator is responsible for observing and recording AEs (including SAEs) and other safety information as required by the protocol.

### 9.1 Definitions

#### 9.1.1 Adverse events (AEs)

An adverse event (AE) is an untoward medical condition or worsening of a pre-existing medical condition that occurs after the use of a drug, whether related to the study drug or not. An AE may be a diagnosis or, in the absence of a diagnosis, a symptom (e.g., nausea, chest pain), a sign (e.g., tachycardia, hepatomegaly), or an abnormal test result (e.g., laboratory test, ECG, etc.). If a diagnosis is later available, the diagnosis will be applied instead of symptoms, signs, or abnormal test results.

The term AE includes both serious and non-serious adverse events.

#### 9.1.2 Serious adverse events (SAEs)

An AE is considered as an SAE when it meets one or more of the following criteria:

- Resulting in death,
- Life-threatening--Note: "Life-threatening" refers to any event that, in the opinion of the investigator, causes the subject to be at risk of death immediately due to the reaction, and does not include an event that has a potential to cause death if it is more severe. For example, drug-induced hepatitis that does not result in liver failure cannot be considered life-threatening because it may be fatal.
- Resulting in hospitalization or prolongation of existing hospitalization--Note: In general, inpatient hospitalization specifically refers to that patients or subjects stay (usually involving at least one stay overnight) in the hospital or emergency room and require observation and/or treatment, which is not performed in the physician's office or outpatient department. Complications that occur during hospitalization are AEs. This event is serious if a complication prolongs the time for the primary treatment, or meets other criteria for seriousness. When in doubt as to whether "hospitalization" occurred or is necessary, the AE is considered serious. Hospitalization for a condition that has already existed and does not worsen from baseline is not considered an AE. Hospitalization or prolongation of current hospitalization due to elective surgery, routine clinical procedures, social reasons, or personal convenience reasons need not be recorded as an AE. However, if the event meets the AE definition, it still needs to be reported as a "serious" or "non-serious" AE according to the usual criteria.
- Resulting in persistent or significant disability/incapacity--Note: The term disability is a substantial disruption of the patient's ability to carry out normal life functions.
- Congenital anomaly/birth defect.

[figure not shown]

- Important medical event: Based on reasonable medical and scientific judgment, events that may not be immediately life-threatening or result in death or hospitalization but might jeopardize the patient or might require intervention to prevent one of the other outcomes listed in the definition above. For example, rescue therapy administered due to allergic bronchospasm in the emergency room or at home, serious hematologic disorder or convulsions not resulting in hospitalization, those leading to drug dependence or abuse, etc.

## **9.2 Collection and Reporting of AEs**

All AEs required to be collected by the protocol must be recorded in the CRF.

### **9.2.1 Time frame for collection of AEs**

AEs/SAEs in this study will be collected from the patient's giving informed consent until 30 days after the last dose.

### **9.2.2 Follow-up of AEs**

After the initial AE/SAE report is submitted, the investigator is required to proactively follow up with each patient and provide further information to the sponsor.

From the perspective of protecting subject's safety, the investigator must follow up all AEs until the final outcome or a stable condition. Follow-up information on AEs obtained after the end of the study (e.g. after database lock) does not necessarily need to be recorded in the CRF. If necessary, the sponsor reserves the right to obtain additional follow-up information of subjects whose AE is persistent at the end of the study. Follow-up information on SAEs occurring after database lock should be reported to the Sponsor's pharmacovigilance team. The investigator should ensure that follow-up provides all supplementary information that clarifies the causality and nature of AEs or SAEs. This may include additional laboratory tests, clinical investigations or consultations with specialists in other health care facilities.

If a patient dies during the clinical trial period or during the protocol-specified follow-up period, the sponsor has the right to obtain disease course information related to the death, including histopathological results.

### **9.2.3 AEs based on examinations and tests**

Examination and laboratory abnormalities (e.g., hematology, serum chemistry, urinalysis, ECG, physical examination, and vital signs) identified at screening will be considered present before the signing of ICF and not be recorded as AEs. Abnormalities with clinical significance at screening can be recorded as related medical histories according to the medical judgment of the investigator.

Any abnormal laboratory finding (e.g., clinical chemistry and hematology) or deterioration in vital signs that is judged by the investigator to be clinically significant will also be recorded as an AE/SAE if it meets the definition in Section 9.1. The investigator will determine if an

[figure not shown]

abnormal laboratory finding or other abnormal assessment is clinically significant with his/her medical and scientific judgment. If the abnormality is associated with clinical signs/symptoms, then the signs/symptoms should be reported as AEs/SAEs and the relevant laboratory values/vital signs as supplementary information. An examination or test abnormality that meets any of the following will generally be considered clinically significant and will be reported as an AE:

- This abnormality suggests a new or worsening disease or organ toxicity from baseline;
- This abnormality needs dose and administration adjustment of the study drug, such as change of dose, drug withdrawal, etc.;
- This abnormality requires additional active intervention, such as increase or change of concomitant medications, close observation, more frequent follow-up assessments, and further diagnostic tests, etc.

Laboratory test values with a clear relationship to progressive disease or deterioration of vital signs will not be reported as AEs/SAEs.

#### **9.2.4 Treatment failure or PD**

The “treatment failure” itself is not reported as an AE. Signs and symptoms or clinical sequelae resulting from treatment failure will be reported if they meet the definition of an AE or SAE (including description).

Specific disease progression won't be reported as an AE. Assessment of PD should be recorded in the corresponding module of the CRF, not the AE module. Signs and symptoms or clinical sequelae resulting from PD should be reported if they meet the definition of an AE or SAE.

#### **9.2.5 Severity grading of AEs**

The severity of all AEs and laboratory abnormalities will be graded according to NCI CTCAT v4.03. For AEs that cannot be graded according to NCI CTCAT v4.03, the severity of each AE will be summarized by clinical description, respectively:

- Grade 1: Mild; asymptomatic or mild symptoms; clinical or diagnostic observations only; or intervention not indicated.
- Grade 2: Moderate; minimal, local or noninvasive intervention indicated; limiting age-appropriate instrumental ADL (For example, shopping for groceries or clothes, using the telephone, managing money, etc.).
- Grade 3: Severe or medically significant but not immediately life-threatening; hospitalization or prolongation of hospitalization indicated; disabling; limiting self care ADL (For example, bathing, dressing and undressing, feeding self, using the toilet, taking medications), and not bedridden.
- Grade 4: Leading to life-threatening consequences; and emergency treatment is needed.

[figure not shown]

- Grade 5: Death related to AEs.

Attention should be paid to distinction of severity and intensity of an AE. The term “severe” is used to describe the intensity of an event, which does not necessarily have to be a serious adverse event (SAE). For example, headache may be severe in intensity (Grade 3), but not necessarily a serious adverse event, unless it meets the criteria of serious adverse events.

### **9.2.6 Correlation between an AE and the study drug**

Investigators should evaluate the causal relationship of each case of AE to the study drug based on medical and scientific judgment with reference to the following criteria:

- (1) Related: occurrence of the event has reasonable temporal relationship with administration, and the event is consistent with known property of the investigational drug, which is improved after dose reduction or interruption and recurs after re-administration and the subject's clinical condition or other treatments can not explain the event.
- (2) Possibly related: occurrence of the event has reasonable temporal relationship with administration, the event is consistent with known property of study drug, and the subject's clinical condition or other treatment may also cause the event.
- (3) Unlikely related: the temporal relationship between the occurrence of the event and administration is uncertain, and the event is not likely to be consistent with known property of the study drug, and the subject's clinical condition or other treatment may also cause the event.
- (4) Not related: occurrence of the event has no reasonable temporal relationship with administration, the event is not consistent with known property of the study drug, and the subject's clinical condition or other treatment may also cause the event. The event lessens or disappears when the disease condition is improved or other treatment is discontinued.

